### Randomization

Randomization will be performed on-line via a secure internet facility in a 1:1 ratio by the TENALEA Clinical Trial Data Management System using randomly permuted blocks with maximum block size 4 within strata formed by nine spiritual counsellors. The researcher contacts the randomization website after patients have signed informed consent. The researcher enters the patient into the randomization program linked to the spiritual counsellor of the patients' hospital. In case in a specific hospital more than one spiritual counsellor is involved in the study a counsellor from that hospital is randomly allocated to the patient. Then the researcher receives the random treatment allocation (intervention versus control) for the patient.

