### Sample size calculation

The primary aim of our study is to improve quality of life and spiritual wellbeing. We will conduct a mixed design measures ANOVA to detect differences between the control-group and the intervention-group over pre-, post- and follow-up measurement. To detect a small effect (effect size f = .10) with statistical power 80%, alpha 5%, and a correlation between repeated assessments of r = .63, we need a sample of 122 patients. With an expected drop out of 20%, we will include 153 patients.

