Potential limitations of our study can be identified. The success of this study critically depends on the skills of the spiritual counsellors participating in the trial. However, spiritual counsellors involved in the study will all be experienced in patient care and will be trained to work with the interview model and e-application. This study will be conducted as a multicentre study, involving academic as well as peripheral hospitals. Therefore, we expect the generalizability of our results to be high. Nevertheless, generalizability will be limited by the national context of the study. In conclusion, by the conduction of this randomized controlled trial we aim to show the effectiveness oft a brief intervention that addresses spiritual concerns of cancer patients to improve quality of life.

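### Nine counsellors are both the randomization strata and the deliverers of the intervention, but the stated ANOVA names only group and time, and the 122 patients assume no counsellor effect on change

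*Protocol article*

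**What the plan says.** Under Randomization, patients are allocated 1:1 "using randomly permuted blocks with maximum block size 4 within strata formed by nine spiritual counsellors". Each patient, in either arm, is linked to a counsellor of their own hospital before the allocation is revealed. Where a hospital has more than one counsellor, one is assigned at random.

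Under Intervention, a spiritual counsellor conducts both consultations. Controls receive care as usual (Abstract; Methods/Design). Counsellor is therefore the only stratification factor in both arms and the delivery cluster in one.

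The only analysis text is in Sample size calculation: "We will conduct a mixed design measures ANOVA to detect differences between the control-group and the intervention-group over pre-, post- and follow-up measurement". The inputs are f = .10, 80% power, 5% alpha and "a correlation between repeated assessments of r = .63, we need a sample of 122 patients", followed by "With an expected drop out of 20%, we will include 153 patients". No counsellor or hospital term, ICC or design effect is mentioned there.

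The Discussion lists as a potential limitation: "The success of this study critically depends on the skills of the spiritual counsellors participating in the trial". It answers this by noting that the counsellors are experienced and will be trained.

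**The concern.** A design stratified by counsellor and delivered by counsellor has two features that an analysis with only group and time does not see.

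- **Stratification.** Stratified blocks balance the arms within each counsellor. If strata differ in how patients change over time, that variation stays in the error term of an unadjusted model although the design has removed it from the comparison. The standard error is then too large and the test conservative.
- **Delivery.** Intervention patients who share a counsellor may share part of the effect. If the effect varies between counsellors, these patients are not independent. The standard error is then too small and the test anti-conservative.

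These are different variance components with opposite signs, and nothing makes them cancel. At stake are the stated power and, to a lesser degree, the nominal 5% level of the test on both primary endpoints.

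**Working it through.** **Inputs from the protocol article.** f = .10, alpha .05, power .80, r = .63, N = 122 analysed, 20% dropout, 153 enrolled (Sample size calculation); two arms 1:1 and nine counsellors (Randomization); three measurements. **Assumed:** ICC of .02, .05 or .10 in the change scores of the intervention arm, because the documents give none.

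**1. Reproduce the stated sample size.** For the group-by-time interaction with sphericity, λ = f²·N·m/(1 − r), with df1 = (2 − 1)(3 − 1) = 2 and df2 = (N − 2)(3 − 1).

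- N = 122: λ = .01 × 122 × 3 / .37 = 9.89, df 2 and 240, power .806.
- 122 is the smallest even N that reaches .80, and 122/.80 = 152.5, rounded up to 153.
- Variants that do not give 122: two measurements (148), between-group main effect with three measurements (594), alpha .025 (144).

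So 122 comes from a group-by-time test of independent patients, with no allowance for counsellor.

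**2. What can affect that test.** The interaction compares changes over time. A counsellor or hospital difference that is constant over time cancels within each patient. Only counsellor differences in change, or in the effect of the intervention on change, matter.

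**3. Delivery clustering in one arm.** Analysed intervention patients per counsellor: c = 61/9 = 6.78. Design effect in that arm: DE = 1 + (c − 1)·ICC. Variance inflation of the arm difference: V = (1 + DE)/2. Power uses λ/V. Type I error of a test that ignores clustering, by a 1-df normal approximation: 2(1 − Φ(1.96/√V)).

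| Assumed ICC | DE | V | SE ratio √V | Power | Type I, formula | Type I, simulated |
|---|---|---|---|---|---|---|
| 0 | 1 | 1 | 1 | .806 | 5% | 4.8% |
| .02 | 1.116 | 1.058 | 1.03 | .78 | 5.7% | 5.8% |
| .05 | 1.289 | 1.144 | 1.07 | .75 | 6.7% | 6.2% |
| .10 | 1.578 | 1.289 | 1.135 | .69 | 8.4% | 8.8% |

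The simulation used a change score for 122 patients, nine counsellors, blocks of 4, no average effect and 8,000 runs. The power column only scales λ. It does not charge for the few degrees of freedom that nine counsellors give a random-effect analysis, so it is if anything slightly favourable.

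**4. Stratification ignored.** If strata explain a share s of the variance of change, the unadjusted standard error is too large by 1/√(1 − s): 1.026 at s = .05 and 1.054 at s = .10. Simulated type I error was 4.1% and 4.0%.

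**5. Does a fixed stratum factor cure delivery clustering?** No. With fixed counsellor effects in the model, simulated type I error was 6.3% at ICC .05 and 9.1% at ICC .10, much the same as without them.

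**6. If nobody drops out.** N = 153 gives c = 76.5/9 = 8.5 and λ = .01 × 153 × 3 / .37 = 12.41. At ICC .05, V = 1.1875 and power is .83. Cluster size and λ must come from the same N. Combining clusters of 8.5 with λ = 9.89 gives .73, which describes neither case.

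**The case against.** The strongest reply is that this is a condensed article. Its analysis is one sentence inside the sample size section, which names a model family and does not list terms. A mixed ANOVA can carry a stratum factor, and adjustment terms are commonly left to the analysis plan. A reader might infer that the final analysis omits the strata. The documents do not show that, so the point is about the model as stated. The sample size is different: it is given in full, and it reproduces only without a counsellor effect.

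A reader might also infer that the standard errors are wrong. That depends on counsellor variation whose size the documents do not give. The Discussion's remark on skill is not evidence of such variation, and the training is meant to reduce it. It does show that the authors think counsellor could matter, while the calculation sets the effect to zero.

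Two further readings go too far. One is that all hospital or counsellor differences inflate the error term, when stable level differences cancel. The other is that power falls to .73 at ICC .05, when the consistent figures are .75 with 122 analysed and .83 with 153.

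Finally, if inference is meant only for these nine counsellors, the clustering argument weakens. However, the Discussion expects high generalizability and foresees implementation in usual care, which points to counsellors beyond the nine.

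**Conclusion.** The point holds in a limited form. The model as stated does not reflect the stratification or the delivery structure, and the 80% power rests on an unstated assumption of no counsellor effect on change. The size is modest: with 122 analysed patients, power drops by about two points at ICC .02, six at .05 and eleven or twelve at .10. A test that ignores delivery clustering has a type I error of roughly 6–7% at ICC .05. Ignoring the strata works the other way and costs 3–5% in standard error if strata explain 5–10% of the variance of change.

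These figures rest on assumed ICCs and variance shares, equal numbers per counsellor, clustering in the intervention arm only, and sphericity. The type I figures come from single-contrast approximations, not from the 2-df test itself. No error in the trial's results is shown. The improvement is worth making because it costs very little.

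**What to change.** 1. In the primary model for both endpoints, include counsellor stratum (nine levels) and its interaction with time. A stratum main effect alone does not bear on a group-by-time test. Equivalently, include counsellor stratum in a baseline-adjusted model.
2. Pre-specify a sensitivity analysis with a random counsellor effect on the intervention-by-time contrast, or cluster-robust standard errors with a small-sample correction. The fixed stratum factor does not address delivery clustering. If inference is intended only for these nine counsellors, say so.
3. In Sample size calculation, state that the 80% power assumes no counsellor effect, and give power at ICC .02–.05 (about .78 to .75 with 122 analysed).

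Cost: wording and one extra analysis. Counsellor is already recorded at randomization. The stratum factor takes 8 of the 122 − 2 = 120 between-patient degrees of freedom, and its interaction with time takes 8 × 2 = 16 of 240. The stated power becomes slightly less favourable.

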### Ethical and legal considerations

The Medical Ethics Review Committee of the Academic Medical Centre Amsterdam confirmed that the Medical Research Involving Human Subjects Act (WMO) does not apply to our study and therefore an official approval of this study by the committee was not required. (Letter, June, 27^th,^, 2012)

## Discussion

This is the first randomized controlled trial to evaluate the role of an assisted structured reflection on life events and ultimate life goals to improve patients’ quality of life and spiritual wellbeing. Insight into one’s ultimate life goals is expected to help patients to integrate a life event such as cancer into their lives. A prospective study in patients is needed to empirically examine whether insight into one’s ultimate life goals improves quality of life and spiritual wellbeing. Since the intervention is brief and based on concepts and skills that spiritual counsellors are familiar with, it can be easily implemented in usual patient care and incorporated in guidelines on spiritual care [2].

Although we expect to find a positive outcome of our intervention on quality of life and spiritual wellbeing, we do realize that negative experiences may also be induced. For example, patients can become anxious or depressed when they bring life events from the past back into their memories [53,54]. We believe it is of utmost importance to assess the effects of our intervention therefore we will also measure for anxiety and depression.

Health care can benefit from technical innovations [55]. In our study we will use an e-application to support the analyses of the spiritual counsellor in a visually attractive way. The e-application will help obtaining a clearer view of the consultations’ content. Afterwards when patients receive the second questionnaire they also receive a printed version of the counsellor’s analysis. This printed version gives patients the opportunity to continue reflecting on their lifelines, interpretations of life events, life goals and the coherence between this all. Additionally, family and friends can have a look at this summary and discuss the results together, which may be of further benefit to the patients and their families.

As a result of this study, spiritual counsellors may be become more structurally involved in the health care of cancer patients. Referral to spiritual counsellors is already explicitly included in guidelines such as the NCCN guideline on distress [1]. However, in clinical practice only few spiritual counsellors are an integral part of the clinical team. We believe that evidence-based interventions on spiritual care will further improve the professionalization of spiritual counselling and structural incorporation into daily patient care.

Potential limitations of our study can be identified. The success of this study critically depends on the skills of the spiritual counsellors participating in the trial. However, spiritual counsellors involved in the study will all be experienced in patient care and will be trained to work with the interview model and e-application. This study will be conducted as a multicentre study, involving academic as well as peripheral hospitals. Therefore, we expect the generalizability of our results to be high. Nevertheless, generalizability will be limited by the national context of the study. In conclusion, by the conduction of this randomized controlled trial we aim to show the effectiveness oft a brief intervention that addresses spiritual concerns of cancer patients to improve quality of life.

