**Methods/Design:**

Based on the findings of our previous research, we have developed a brief interview model that allows spiritual counsellors to explore, explicate and discuss life events and ultimate life goals with cancer patients. To support the interview, we created an e-application for a PC or tablet. To examine whether this assisted reflection improves quality of life we will conduct a randomized trial. Patients with advanced cancer not amenable to curative treatment options will be randomized to either the intervention or the control group. The intervention group will have two consultations with a spiritual counsellor using the interview scheme supported by the e-application. The control group will receive care as usual. At baseline and one and three months after randomization all patients fill out questionnaires regarding quality of life, spiritual wellbeing, empowerment, satisfaction with life, anxiety and depression and health care consumption.

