## Methods/Design

This study primarily aims to answer the following question: does an assisted structured reflection on life events and ultimate life goals of cancer patients improve quality of life? To evaluate the effect of the structured reflection we will conduct a multicenter two-armed randomized non-blinded controlled trial. Previous randomized studies on spiritual interventions in cancer patients have included patients from hospices or palliative care units [31-34]. However, spirituality is not restricted to end of life [35]. Therefore, in this study we will include patients who have been confronted with advanced cancer, but still have a life expectancy of at least half a year. The following inclusion and exclusion criteria apply:

Inclusion criteria

1. Patients ≥ 18 years of age with advanced cancer not amenable to curative treatment.

2. Life expectancy ≥ 6 months.

Exclusion criteria

1. Karnofsky Performance Score < 60.

2. Insufficient command of the Dutch language to fill out Dutch questionnaires.

3. Current psychiatric disease.

Eligible patients will be invited by their treating oncologists and asked to give written informed consent. A baseline assessment will take place in consenting patients, including an evaluation of quality of life and spiritual wellbeing. Within two weeks after the baseline assessments patients will be randomized between an intervention and a control group (care as usual) (Figure 1).

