**Figure 1 F1:**
[figure not shown]
Study flow-chart.

Two months and four months after randomization, patients of both the intervention and the control group will complete questionnaires regarding quality of life, spiritual well being, empowerment and health care consumption. In the intervention group we will also conduct a telephone evaluation to examine the satisfaction with the intervention.

Patients declining participation will be asked to answer a few questions by telephone, to explore whether participants and non-participants differ.

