### Intervention

We have developed a semi-structured interview model for the interpretation of contingent life events in life stories, based on literature on the experiences of contingency and the importance of ultimate life goals. In this interview we inquire into (a) the life events, (b) ultimate life goals, (c) the interpretation of contingent life events (d) reconstruction of life story. Since 2008 this interview model has been used in various populations, including mentally handicapped people, young people with problem behavior, individuals > 30 years, highly qualified young people in their twenties, Zen meditation trainees, volunteers in hospices, cancer patients, primary school teachers, and asylum seekers [24]. The respondents were from a religious and non-religious background. In all populations, the interviews were evaluated positively by most of the respondents. They did not experience the semi-structured nature of the interview as a drawback and frequently indicated that it was a very special experience to reconstruct their life stories in collaboration with an interviewer. In the experimental arm of our randomized study we will use this interview model for an assisted, structured reflection on contingent life events and ultimate life goals, which will be supported by a newly developed e-application. The assisted reflection is carried out in two consultations with a spiritual counsellor. The counsellor analyses the first consultation in the interim and discusses this analysis with the patient during the second consultation (Table 1).

**Table 1 T1:** Summary of the intervention

**Consultation I**	**Analysis**	**Consultation II**
**Patient and spiritual counsellor**	**Spiritual counsellor**	**Patient and spiritual counsellor**
- Draw a life line	- Analyse life line	- Reflect on life line
- Explicate the most important events	- Analyse important life events	- Reflect on most important events
- Define the most important events	- Analyse life goals	- Reflect on life goals
- Draw a life line for the future	- Define coherence and tension between life goals and life events	- Discuss and reflect on tension and coherence between life goals and life events
- Define life goals		- Reconstruct life story

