### Endpoints

#### Primary endpoints

Two primary endpoints are distinguished. First, general quality of life as measured with the general quality of life scale of the European Organization for Research and Treatment of Cancer Quality of Life Questionnaire-Core 15 Palliative Care (EORTC QLQ-C15-PAL). The EORTC QLQ-C15-PAL is a shortened version of the EORTC QLQ-C30, which is one of the most rigorously studied and widely used health-related quality-of-life questionnaires in oncology research [38-41].

Second, spiritual wellbeing as measured by the subscale meaning/peace of the Functional Assessment of Chronic Illness Therapy - Spiritual wellbeing 12 (FACIT-Sp12). The FACIT-Sp-12 is a widely used measure and is not restricted to a particular religion and is valid and reliable [42]. The FACIT-sp-12 demonstrates good internal consistency reliability and a significant relation with quality of life in a large, multiethnic sample [43,44].

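### The printed counsellor's analysis reaches intervention patients together with the second questionnaire, so the self-reported primary endpoints are measured under different conditions in the two arms at that assessment

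*Protocol article*

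**What the plan says.** The relevant statement is in the Discussion of the protocol article: "Afterwards when patients receive the second questionnaire they also receive a printed version of the" counsellor's analysis. The next sentence gives its purpose: "This printed version gives patients the opportunity to continue reflecting on their lifelines, interpretations of life events, life goals and the coherence between this all". The Discussion adds that family and friends may look at the printout and talk it over.

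The printed analysis is a product of the experimental arm. Under Intervention: "The counsellor analyses the first consultation in the interim and discusses this analysis with the patient during the second consultation". For the other arm the Abstract says: "The control group will receive care as usual". Table 1, which summarises the intervention, lists two consultations and the analysis between them but no printout.

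Methods/Design describes a "multicenter two-armed randomized non-blinded controlled trial". There are two primary endpoints, both questionnaire scales. The first is introduced with "First, general quality of life as measured with the general quality of life scale of the European Organization for Research and Treatment of Cancer"; the second is the meaning/peace subscale of the FACIT-Sp-12. The text under Figure 1 has patients in both arms complete the follow-up questionnaires. Sample size calculation plans a mixed-design ANOVA comparing the arms over pre-, post- and follow-up measurement.

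**The concern.** A between-arm comparison of self-reported scores is fair only if the scores are collected in the same way in both arms. Here one arm receives the instrument alone. The other receives it with a personal summary of life line, life goals and how they fit together, which is meant to prompt reflection. One of the two primary scales asks about meaning and peace, the very subject of that summary.

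Patients in an open trial know their allocation, and that cannot be helped. A cue that arrives with the measuring instrument in one arm only can be helped. If answers at that assessment shift because the document has just arrived, the shift enters the post-treatment term of the planned ANOVA. At that assessment nothing in the design distinguishes it from an effect of the two consultations.

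**Working it through.** **1. Is the printout confined to one arm?** The Discussion sentence speaks of patients without naming an arm. The analysis is made from consultation I, which only the intervention arm has. Controls receive usual care, and no section gives them comparable material. So the printout can reach intervention patients only.

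**2. Which assessment is affected?** There are three: baseline and two follow-ups. With baseline as the first questionnaire, the second is the first follow-up. The Abstract dates the follow-ups at one and three months and the text under Figure 1 at two and four months. That conflict leaves the date of the affected assessment unclear but does not change which one it is. Co-delivery is not described for the last assessment.

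**3. Reproducing the plan's sample size.** Inputs from Sample size calculation: f = 0.10, power 80%, alpha 5%, r = 0.63 and 20% dropout. There are k = 2 arms and m = 3 assessments. For the group-by-time interaction:

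- λ = f² · N · m / (1 − r) = 0.01 × 122 × 3 / 0.37 = 9.89
- df1 = (k − 1)(m − 1) = 2 and df2 = (N − k)(m − 1) = 240
- Power at N = 122 is 0.806. The smallest N reaching 80% is 121, or 122 with equal arms.
- With dropout: 122 / 0.8 = 152.5, so 153.

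The plan's 122 and 153 are reproduced and are not in dispute.

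**4. What f = .10 means in SD units.** Let d_t be the between-arm difference in SD at assessment t, and d̄ its mean over the three assessments. The interaction variance over the six cells is Σ(d_t − d̄)² / 12, and f is its square root.

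- Difference b at one follow-up only (0, b, 0): Σ = 2b²/3, so f = b/√18.
- Equal difference at both follow-ups (0, b, b): Σ = 2b²/3, so again f = b/√18.
- Linear build-up (0, b/2, b): Σ = b²/2, so f = b/√24.

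For f = 0.10 the first two patterns give b = 0.10 × √18 = 0.424 SD. The third gives 0.10 × √24 = 0.49 SD at the last assessment. The plan states only f and no pattern, so 0.42 SD holds for the first two.

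**5. Scale under assumed shifts.** The shifts below are assumptions; the documents give none.

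- 0.1 / 0.424 = 24%
- 0.2 / 0.424 = 47%

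Put another way, suppose there is no true effect and the intervention arm shifts by b SD at the second questionnaire only. At N = 122, the chance of a significant group-by-time result is then:

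| Assumed b (SD) | f = b/√18 | Chance of p < 0.05 |
|---|---|---|
| 0 | 0 | 5.0% |
| 0.1 | 0.0236 | 9.3% |
| 0.2 | 0.0471 | 24% |

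Because the interaction test has no direction, these chances are the same whether the shift raises or lowers scores.

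**The case against.** The strongest reply is that the printout belongs to the intervention. It is presented as a means of continued reflection, so its effect would be part of the treatment effect and not bias. It is also not new to the patient, since the analysis was already presented and discussed in the one-hour Consultation II. Patients know their allocation anyway, and the article does not say when they read the printout. The source is one descriptive sentence in the Discussion.

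Much of this stands as a limit. Any lasting benefit of the printout may fairly be counted with the package, and the added contrast may be small. It does not settle the timing. Even as part of the package, a document that arrives with the questionnaire can produce a momentary response in one arm, and at that assessment such a response looks the same as an effect of the consultations. The sentence states a procedure, so following the article as written creates the asymmetry.

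Two stronger readings are tempting but not supported:

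- A reader might infer that the bias favours the intervention. The documents do not show this. The same Discussion warns that bringing past life events back to mind can make patients anxious or depressed, so scores could also fall.
- A reader might also object to the satisfaction call, because "In the intervention group we will also conduct a telephone evaluation to examine the satisfaction with the intervention" gives no order relative to the questionnaires. That is a logistical detail which an article may leave to the full protocol, and the sentence itself states nothing wrong.

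**Conclusion.** The point holds in a limited form. As written, the second questionnaire is completed under different conditions in the two arms, in a non-blinded trial whose two primary endpoints are self-reported. Any momentary response to the printout could bias the comparison at that assessment in either direction and cannot be separated there from the effect of the consultations.

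A reader might infer that the whole trial result is compromised. The documents do not support that: co-delivery is stated for one assessment only, so a lasting effect can still be examined at the last one.

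Neither the size nor the direction of any bias can be derived from the documents. The 24% to 47% range rests on an assumed shift of 0.1 to 0.2 SD, and on f = .10 being read as a difference at one follow-up or an equal difference at both. The conclusion also rests on counting baseline as the first questionnaire. The case for acting is that the asymmetry is avoidable at little cost.

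**What to change.** Send the second questionnaire identically in both arms, with nothing enclosed for intervention patients that controls do not get. Replace the Discussion sentence with one saying that intervention patients are sent the printed analysis separately, after the second questionnaire has been returned or its return window has closed. Merely deleting the reference to the second questionnaire would leave the printout with no timing at all. The window clause ensures that patients who do not return the questionnaire still receive their printout.

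The second assessment would then precede the printout for every patient who responds within the window.

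The cost is one extra mailing to intervention patients, a short delay before they receive the printout, and one rewritten sentence. The sample size and the planned analysis are unaffected.
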